## 4 STUDY DESIGN

This study is a three-stage cluster randomized historically controlled crossover trial designed to evaluate the feasibility of the implementation of two AS strategies. Data will be obtained from four community hospitals in three stages. In stage 1, historical data from each hospital will be collected for the year prior to study initiation from all participating hospitals. These data are used as a control representing current practice. In stage 2, the four hospitals will be divided into two pairs based upon bed size. One hospital from each pair will be randomly assigned to a six-month period of antimicrobial restriction and preauthorization (Strategy 1; stage 2) followed by a six-month period of post-antibiotic prescription review (Strategy 2; stage 3). The other two hospitals will undergo Strategy 2 in stage 2 followed by Strategy 1 in stage 3 to help alleviate the concern for seasonal/temporal effects when comparing the strategies to each other. Temporal/seasonal effects are not controlled when comparing to the historical control. A one-month wash out will be performed between each stage. Three antibiotics will be specifically targeted for intervention: anti-pseudomonal carbapenem of choice at the study hospital, vancomycin, and piperacillin-tazobactam. Utilization of alternative antimicrobials, including fluoroquinolones, cephalosporins, and anti-methicillin-resistant *Staphylococcus aureus* (anti-MRSA) systemic antimicrobials (e.g., nafcillin, daptomycin, linezolid, ceftaroline, clindamycin, and trimethoprim-sulfamethoxazole [TMP-SMX]) will also be collected.

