## 9 STATISTICAL CONSIDERATIONS

### 9.1 Design and Sample Size Considerations

This is a feasibility study to evaluate if four hospitals can implement two antimicrobial stewardship interventions. Analysis of the primary feasibility components will be descriptive (a summary as to whether each hospital was able to successfully implement each of the interventions). No hypothesis testing will be completed for these summaries.

The secondary stewardship analyses may include hypothesis testing and estimation of the difference to the control as well as between the two stewardship strategies.

This study will collect data on all patients prescribed a targeted or alternative antibiotic at each of four hospitals, except patients who receive < 24 hours of surgical prophylaxis. The three targeted antibiotics are:

- Anti-pseudomonal carbapenem of choice at the study hospital
- Vancomycin
- Piperacillin-tazobactam.

The alternative antimicrobials of interest are:

- Fluoroquinolones
- Cephalosporins
- anti-MRSA systemic antimicrobials (e.g., nafcillin, daptomycin, linezolid, ceftaroline, clindamycin, and TMP-SMX).

This study will not target a specific number of patients to enroll. Instead, it will be conducted for specific periods of time. Each hospital will implement its first strategy for six months, followed by an one-month period with no strategy, and then a second, six-month period for the second strategy, for a total duration of 13 months. Additionally, one year of historical data from the four hospitals will be analyzed.

Although this study does not target a specific number of participants, hospitals are expected to admit at least 600 patients per month. Thus, we expect to have at least 3600 patients included in analyses for each six-month intervention period. When conducting within-hospital analyses, a conservative sample size of 3000 patients during each intervention period will achieve 97% power to detect a difference between the group proportions (e.g., of patients with no [0] DOT) of 0.0500 when the proportion in one group is 0.50 using an alpha of 0.05. The power for detecting a difference as a function of sample size is illustrated in Figure 9-1:

Figure 9-1:

[figure not shown]

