#### 6. Hospital Admissions

**Purpose:** To summarize hospital admissions over the time periods of interest.

Hospital Admissions Tables, by hospital

a. Number of unique admissions by hospital

1. In the year preceding the start of the study period 1 (October 6, 2013 through October 5, 2014)
2. Study period 1 (October 6, 2014 through April 3, 2014)
3. Study period 2 (May 4, 2015 through October 30, 2014)

b. Number of admissions by hospital that received an “Included antibiotic” or “other antibiotic”

1. In the year preceding the start of the study period 1 (October 6, 2013 through October 5, 2014)
2. Study period 1 (October 6, 2014 through April 3, 2014)
3. Study period 2 (May 4, 2015 through October 30, 2014)

c. Number of admissions by hospital that received an “Included antibiotic”

1. In the year preceding the start of the study period 1 (October 6, 2013 through October 5, 2014)
2. Study period 1 (October 6, 2014 through April 3, 2014)
3. Study period 2 (May 4, 2015 through October 30, 2014)

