408         than one intervention over the course of a year)

409 Signs and symptoms

410     • Fever

411     • Leukocytosis

412     • Hypotension

413     • Cough or Sputum production

414     • Other signs or symptoms

- 415 • List of other/specifies
- 416 • Number of signs and symptoms per intervention

417 Culture data

- 418 • Culture data available for review (yes/no)
- 419 • If yes, was the culture data reviewed
- 420 • If yes, did it help inform the recommendation?

421 Intervention outcome

- 422 • Was the recommendation followed?
- 423 • Was there an ID consult after the intervention?
- 424 • ICU admission

425 Ultimate Infection diagnosis related to recommendation

- 426 • Pneumonia
- 427 • UTI
- 428 • Meningitis
- 429 • Surgical site infection
- 430 • SSTI
- 431 • Colitis
- 432 • Bacteremia
- 433 • Sepsis with unknown source
- 434 • No infection
- 435 • Other
- 436 • List of other, specify

437 **10. Days Of Therapy**

438 **Purpose:** To address Secondary objective 2, to compare DOT for antibiotics of interest between each  
439 strategy.

440

- 441 • Days of therapy (DOT) for targeted and alternative antibiotics
  - 442 ○ Per the protocol, DOT will be measured as the number of days a patient receives
  - 443 each targeted and alternative antibiotic during the hospital admission

444 The three targeted antibiotics are:

- 445 • Anti-pseudomonal carbapenem of choice at the study hospital
- 446 • Vancomycin
- 447 • Piperacillin-tazobactam.

448 The alternative antimicrobials of interest are:

- 449 • Fluoroquinolones
- 450 • Cephalosporins
- 451 • anti-MRSA systemic antimicrobials (e.g., nafcillin, daptomycin, linezolid, ceftaroline,
- 452 clindamycin, and TMP-SMX).

Among admissions with an included antibiotic, by hospital

- Table 1
  - Year prior to study
  - Period 1 Admission with Included antibiotic, no intervention
  - Period 1 Admission with stewardship intervention
  - Period 2 admission with Included antibiotic, no intervention
  - Period 2 admission with stewardship intervention
- Table 2
  - Period 1 (all admissions with an antibiotic of interest)
  - Period 2 (all admissions with an antibiotic of interest)
- Table 3
  - For 3 contrasts (PAR vs Historical year; Res/PreA vs historical Year; PAR vs Res/PreA)
  - Difference in proportion used drug with 95%CI
  - Difference in Mean DOT with 95% CI

For each antibiotic,

- proportion of admissions where the antibiotic was received
- DOT for the antibiotic

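### The SAP's two study windows are printed ending before they begin, and each half-year strategy period is compared, hospital by hospital and unadjusted, with a full 12-month historical year although season-matched control days are already in the data

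*Combined protocol and SAP*

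**What the plan says.** SAP section 6 gives three windows, repeated in each of its three lists. The control is "In the year preceding the start of the study period 1 (October 6, 2013 through October 5, 2014". The strategy periods are "Study period 1 (October 6, 2014 through April 3, 2014" and "Study period 2 (May 4, 2015 through October 30, 2014". The later tables refer to period 1 and period 2 without giving dates again.

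Protocol section 9.1 fixes the intended lengths: "Each hospital will implement its first strategy for six months, followed by an one-month period with no strategy", then six months of the second strategy, 13 months in all. It adds: "Additionally, one year of historical data from the four hospitals will be analyzed".

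Table 3 in SAP section 10 (days of therapy, DOT) is specified as "For 3 contrasts (PAR vs Historical year; Res/PreA vs historical Year; PAR vs Res/PreA", reported as differences in proportions and means with 95% confidence intervals. SAP section 13 repeats the three contrasts for hospital days and ICU admission. Death is named there for summary but has no contrast line. SAP section 3.5 makes analysis by hospital the firm plan; stratified pooling is optional.

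On season, Protocol section 4 says: "Temporal/seasonal effects are not controlled when comparing to the historical control". Protocol section 9.4.3 and SAP section 3.5.2 list temporal bias against the historical control as a limitation.

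On washout, Protocol section 4 says: "A one-month wash out will be performed between each stage". The same section makes the historical data stage 1 and takes them from the year before study initiation. Protocol section 9.1 and SAP section 3.1 describe a washout only between the two strategies.

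**The concern.** Three things in the date definitions affect the historical contrasts.

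- **Printed windows.** They are impossible as written, and they define the analysis periods for every later table.
- **Season.** A hospital's October-to-April strategy, or its May-to-October strategy, is compared with a year containing both halves. Antibiotic use or case mix that varies by season would then appear as a strategy effect. Two of the three planned contrasts are affected, and they bear directly on secondary hypothesis 4 (lower use of targeted drugs than before implementation).
- **Run-up.** The control year ends the day before period 1 starts. Protocol section 4.1.4 places pharmacist training before the study, so some preparation may fall in days counted as current practice. If it already changed prescribing, the contrast would be diluted.

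**Working it through.** **1. Dates.** All counts include both end days, except end minus start.

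| Item | Dates | Days |
|---|---|---|
| Historical year | Oct 6, 2013 to Oct 5, 2014 | 365 |
| Gap before period 1 | none | 0 |
| Period 1 as printed, end minus start | Oct 6, 2014 to Apr 3, 2014 | -186 |
| Period 2 as printed, end minus start | May 4, 2015 to Oct 30, 2014 | -186 |
| Period 1, end year read as 2015 | Oct 6, 2014 to Apr 3, 2015 | 180 |
| Gap on that reading | Apr 4 to May 3, 2015 | 30 |
| Period 2, end year read as 2015 | May 4 to Oct 30, 2015 | 180 |

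180 + 30 + 180 = 390 days, about 13 months. The 2015 reading fits Protocol section 9.1 and is assumed below.

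**2. Matching days inside the historical year.** For period 1: Oct 6, 2013 to Apr 3, 2014 = 180 days. For period 2: Oct 6 to 30, 2013 (25) plus May 4 to Oct 5, 2014 (155) = 180 days. The two control windows share the 25 October days.

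**3. Size of a seasonal shift (illustration).** The documents give no seasonal data. Assume the outcome is higher by D on Oct 6 to Apr 3 (180 days) than on the other 185 days. D could have either sign.

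- Historical mean, above the low level: 180/365 = 0.493D.
- Period 1 lies wholly in the first block: 1 - 0.493 = **+0.51D**.
- Period 2 has 25 of its 180 days in that block: 25/180 - 180/365 = 0.139 - 0.493 = **-0.35D**.
- With the matched windows, both shifts are 0 under this model: 1 - 1 and 25/180 - 25/180.

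| Assumed D, % of mean DOT | Period 1 | Period 2 |
|---|---|---|
| 5 | +2.5% | -1.8% |
| 10 | +5.1% | -3.5% |
| 20 | +10.1% | -7.1% |

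The shape matters. With an assumed annual cosine of amplitude A peaking between Jan 1 and Feb 15, the shifts are +0.48A to +0.65A and -0.56A to -0.65A; matching brings both to about 0.

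**4. Pooled over both orders, equal weights.** Two-level model: (0.51 - 0.35)/2 = +0.08D. Cosine: -0.07A to +0.04A. Pooling cancels most of the season effect.

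**5. Precision.** The plan's own figure is 97% power for 3000 per period, 0.50 against 0.55, alpha 0.05. A two-sided calculation gives 97.3%, so it is reproduced. On the same planning numbers, a full-year control has about 6000 patients and 99.4% power; a matched control has about 3000 and 97.3%.

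With 3000 against 6000 and a proportion of 0.5, the standard error is sqrt(0.25/3000 + 0.25/6000) = 0.0112. A purely seasonal shift of 1, 2 or 3 points makes the 95% interval exclude zero about 15%, 43% or 77% of the time. Matching raises the standard error to sqrt(0.25/3000 + 0.25/3000) = 0.0129.

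**6. Run-up.** No section dates the training, approvals or IT set-up. Assume the last 30 days before launch, or the 66 days from the synopsis's estimated start (Aug 1 to Oct 5, 2014), carry a fraction f of the full effect, with f from 0.25 to 1.

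- Full-year control: dilution from 0.25 × 30/365 = 2% to 66/365 = 18%.
- Matched period 1 control: none of these days.
- Matched period 2 control: from 0.25 × 30/180 = 4% to 66/180 = 37%. Matching concentrates the run-up here.

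**7. Distance in time.** The midpoint of the historical year lies about 9 months before that of period 1 and 16 months before that of period 2. The matched period 1 control lies 12 months back. The matched period 2 control lies on average (155 × 12 + 25 × 24)/180 = 13.7 months back.

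**The case against.** **The limitation is disclosed and the analyses are secondary.** Both documents warn of temporal bias, and the primary analysis is descriptive. This stands and limits the severity. But disclosure does not remove a mismatch that the existing data can remove.

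**The models adjust for time.** A reader might infer that the Table 3 contrasts are the only assessment of hypothesis 4. They are not: the DOT model in SAP section 10 lists study period, strategy and calendar time. However, it gives no form for calendar time, does not say whether the historical year enters, and does not cover hospital days, ICU admission or death. The exploratory model in Protocol section 9.4.1.3 has a period term but no season term.

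**The crossover deals with season.** Pooled, it largely does, but pooling is optional. Within one hospital it does not.

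**The washout was not broken.** A reader might infer that the SAP drops a promised washout and contaminates its control. The text does not settle this. Protocol section 4 asks for a month between each stage yet also takes stage 1 from the year before initiation, and other sections give a single washout. Before launch there is no strategy to wash out, and any run-up effect on prescribing is inferred. Moving the whole control year back a month is therefore not clearly right either, and that control could still contain run-up days from August 1.

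**The dates are an obvious slip.** Probably so, and a filter that returns no admissions would be noticed. They still need correcting because the SAP defines the periods nowhere else.

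**Conclusion.** The printed windows are wrong as a matter of fact, and the SAP must be corrected. The end year 2015 is the likely reading, not a confirmed one.

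The by-hospital historical contrasts have an avoidable exposure to season. It is tempting to say that season biases them by a known amount, or in a known direction at each hospital. The documents contain no seasonal data, so neither can be claimed. Shifts of +0.51D and -0.35D rest on an assumed two-level season, and the percentages on an assumed D of 5 to 20% of mean DOT.

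The washout wording is inconsistent and needs reconciling; run-up dilution is possible but not shown. The direct comparison of the two strategies does not use the historical year, and the primary feasibility summaries and the 97% power figure are unaffected.

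**What to change.** 1. Check the end dates in all three lists of SAP section 6 against the actual study dates and correct them; 2015 for both fits the design.
2. For the historical contrasts in SAP sections 10 and 13, compare period 1 with October 6, 2013 to April 3, 2014, and period 2 with October 6 to 30, 2013 plus May 4 to October 5, 2014. Keep the full-year contrast as a sensitivity analysis.
3. Reconcile the washout statements in Protocol sections 4 and 9.1 and SAP sections 3.1 and 6, saying whether a gap before period 1 is intended.
4. Add a sensitivity analysis that leaves the run-up out of the control: the last 30 days, or from August 1, 2014. For the matched period 2 contrast, drop the same calendar days from period 2, leaving 150 or 114 days a side, so that the season match is kept.

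The cost is SAP wording and a changed date filter; no new data are needed. Each control window has about half the admissions, so at the planning numbers the confidence interval widens by about 15% (0.0129/0.0112). The period 1 control lies about 12 rather than 9 months back. Secular trend and the drug shortages noted in SAP section 3.5.2 remain.

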## 7. Interventions recorded/tracking of admissions with interventions

### Example content:

**Purpose:** to document the number of interventions performed and the number of unique patients per period/strategy/hospital. To document mis-matches across datasets.

#### Interventions tables

- a. Number of stewardship interventions recorded in REDCap
- b. Number of unique patients
- c. Number of interventions with intervention follow-up information
- d. Number of interventions which match to EHR demographics and antibiotics data
- e. Number of interventions which match to EHR height/weight information

Number of intervention follow-ups recorded that do not match to an Intervention

Number of interventions per patient per study period, by Hospital

## 8. Selected patient characteristics

**Purpose:** to describe the hospital/study population

By Hospital, for the following groups/time periods

- a. Year prior to study
- b. Period 1 Admission with Included antibiotic, no intervention
- c. Period 1 Admission with stewardship intervention
- d. Period 2 admission with Included antibiotic, no intervention
- e. Period 2 admission with stewardship intervention

- 335 • Age/year of birth
- 336 • Race
- 337 • Sex
- 338 • Ethnicity
- 339 • Height (cm)
- 340 • Weight (kg)
- 341 • BMI

## 342 **9. REDCap Intervention summary tables**

343 **Purpose:** to summarize the intervention data

344

- 345 a. For categorical variables: Tables showing categorized N and % within Hospital/Study period
- 346 b. Table summaries include mean, SD, min, 25th, median, 75th, and max

347

348 Intervention contact type

349 Interventions per month (for each strategy, months 1 -6)

350 Contact type by targeted antibiotic

- 351 • Vancomycin yes/no
- 352 • Piperacillin-Tazo yes/no
- 353 • Carbapenem yes/no

354 Targeted Antibiotic Vancomycin

- 355 • Targeted antibiotic Vancomycin (yes/no)
- 356 • If Yes, then
  - 357 ○ Vancomycin Recommendation
  - 358 ○ De-escalation (yes/no)
  - 359 ○ Continue Therapy (yes/no)
  - 360 ○ Changed dose (yes/no)
  - 361 ○ Other
  - 362 ○ List of other, specifies
  - 363 ○ Duration (continuous)

364 Targeted Antibiotic Piperacillin-Tazo

- 365 • Targeted antibiotic Piperacillin-Tazo (yes/no)
- 366 • If yes, then
  - 367 ○ Piperacillin-Tazo Recommendation
  - 368 ○ De-escalation (yes/no)
  - 369 ○ Continue Therapy (yes/no)
  - 370 ○ IV to PO conversion
  - 371 ○ Changed dose (yes/no)
  - 372 ○ Other
    - 373 ■ List of other, specifies
  - 374 ○ Duration (continuous)

375

376 Targeted Antibiotic Carbapenem

377     • Targeted antibiotic Carbapenem (yes/no)

378     • If yes, then

379         ○ Carbapenem Recommendation

380         ○ De-escalation (yes/no)

381         ○ Continue Therapy (yes/no)

382         ○ IV to PO conversion

383         ○ Changed dose (yes/no)

384         ○ Other

385         ○ List of other, specifies

386         ○ Duration (continuous)

387 Indication (all are yes/no)

388     • High risk of MDR infection

389         ○ If yes, then (% among people at high risk of MDR, or % of total?)

390         ○ History of MDR infection

391         ○ Hospitalization in last 90 days

392         ○ LTC facility in last year

393         ○ Antibiotic or chemo in last 30 days

394         ○ Hemodialysis (current)?

395         ○ Other

396         ○ List of other, specifies

397         ○ Empiric need

398         ○ Sepsis

399         ○ Pneumonia

400         ○ UTI

401         ○ Meningitis

402         ○ Surgical Site Infection

403         ○ SSTI

404         ○ Bacteremia

405         ○ Other

406         ○ List of other specifies

407     • Number of indications per intervention (not per person, as a given person could have more  
408         than one intervention over the course of a year)

409 Signs and symptoms

410     • Fever

411     • Leukocytosis

412     • Hypotension

413     • Cough or Sputum production

414     • Other signs or symptoms

- 415 • List of other/specifies
- 416 • Number of signs and symptoms per intervention

417 Culture data

- 418 • Culture data available for review (yes/no)
- 419 • If yes, was the culture data reviewed
- 420 • If yes, did it help inform the recommendation?

421 Intervention outcome

- 422 • Was the recommendation followed?
- 423 • Was there an ID consult after the intervention?
- 424 • ICU admission

425 Ultimate Infection diagnosis related to recommendation

- 426 • Pneumonia
- 427 • UTI
- 428 • Meningitis
- 429 • Surgical site infection
- 430 • SSTI
- 431 • Colitis
- 432 • Bacteremia
- 433 • Sepsis with unknown source
- 434 • No infection
- 435 • Other
- 436 • List of other, specify

437 **10. Days Of Therapy**

438 **Purpose:** To address Secondary objective 2, to compare DOT for antibiotics of interest between each  
439 strategy.

440

- 441 • Days of therapy (DOT) for targeted and alternative antibiotics
  - 442 ○ Per the protocol, DOT will be measured as the number of days a patient receives
  - 443 each targeted and alternative antibiotic during the hospital admission

444 The three targeted antibiotics are:

- 445 • Anti-pseudomonal carbapenem of choice at the study hospital
- 446 • Vancomycin
- 447 • Piperacillin-tazobactam.

448 The alternative antimicrobials of interest are:

- 449 • Fluoroquinolones
- 450 • Cephalosporins
- 451 • anti-MRSA systemic antimicrobials (e.g., nafcillin, daptomycin, linezolid, ceftaroline,
- 452 clindamycin, and TMP-SMX).

Among admissions with an included antibiotic, by hospital

- Table 1
  - Year prior to study
  - Period 1 Admission with Included antibiotic, no intervention
  - Period 1 Admission with stewardship intervention
  - Period 2 admission with Included antibiotic, no intervention
  - Period 2 admission with stewardship intervention
- Table 2
  - Period 1 (all admissions with an antibiotic of interest)
  - Period 2 (all admissions with an antibiotic of interest)
- Table 3
  - For 3 contrasts (PAR vs Historical year; Res/PreA vs historical Year; PAR vs Res/PreA)
  - Difference in proportion used drug with 95%CI
  - Difference in Mean DOT with 95% CI

For each antibiotic,

- proportion of admissions where the antibiotic was received
- DOT for the antibiotic
  - Admissions where the antibiotic was not received will have a DOT of 0.
- Modeling (1 model for each of the antibiotics of interest)
  - The purpose of the model is to look at the effect of the intervention on DOT for each antibiotic of interest
  - Dependent variable = DOT for each antibiotic
  - Adjusting for hospital, study period, AS strategy, calendar time, demographic variables
  - The interactions of study period \* strategy, hospital \* study period, hospital \* strategy, will be explored.

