### 3.1.4 Exploratory Objective

To evaluate the interpretations reached from analysis of data based on traditional (DOT/patient-days) outcomes as compared to newer proposed outcomes (defined in Section 3.1.3 Secondary Objectives, number 5).

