Stewardship Strategy 1 – Antimicrobial restriction and Pre-authorization. Following approval of the protocol at study hospitals, all prescriptions for targeted antibiotics will require phone approval by the trained PharmD. Prescribers will be instructed to discuss the patient details and the rationale for the desired antimicrobial with the PharmD. Specifically, prescribers must contact the pharmacist via pager or phone call to discuss the rationale for using the targeted antibiotic. The pharmacist will discuss the rationale and the specific clinical scenario with the prescriber and will decide if the targeted antibiotic is approved or denied. If the pharmacist denies the use of the targeted antibiotic, the pharmacist will provide recommendations for alternative antibiotics for the specific clinical scenario. The pharmacist will then document this interaction in the REDCap database, documenting which targeted antibiotic was requested, the prescriber’s rationale for requesting the targeted antibiotic, the patient’s symptoms and pertinent

clinical data at the time of the request, whether the request met the criteria for use of the targeted antibiotic (or not), and the pharmacist's recommendation. Prescriptions for targeted antibiotics will be eligible for intervention if written between 7am and 6pm Monday through Friday. Off-hours prescriptions will be reviewed for approval for continuation the following morning.

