#### 9.4.2 Data Acquisition

Cost and feasibility data will be obtained using hospital cost data (antibiotics and pharmacy FTE), questionnaires, and notes/observations created during interactions with hospital personnel. Patient endpoint data will be obtained from electronic pharmacy antibiotic prescribing data (start and stop dates for all antibiotics) and hospital databases (e.g., ADT data for admit/discharge dates for all patients; patient status database (mortality); and diagnosis code databases).

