#### **13. Patient specific outcomes between each strategy**

**Purpose:** to address secondary objective 3, to compare patient-specific outcomes between each strategy, including but not limited to the following:

494 a. Total hospital days

495 b. Intensive care unit admission

496 Each of Total hospital days, death, and ICU admission will be summarized by hospital in 3 tables:

497 Among admissions with an included antibiotic

498 • Table 1

499 ○ Year prior to study

500 ○ Period 1 Admission with Included antibiotic, no intervention

501 ○ Period 1 Admission with stewardship intervention

502 ○ Period 2 admission with Included antibiotic, no intervention

503 ○ Period 2 admission with stewardship intervention

504 • Table 2

505 ○ Period 1 (all admissions with an antibiotic of interest)

506 ○ Period 2 (all admissions with an antibiotic of interest)

507 • Table 3

508 ○ For 3 contrasts (PAR vs Historical year; Res/PreA vs historical Year; PAR vs Res/PreA)

509 ○ Difference in proportion of ICU admissions with 95%CI

510 ○ Difference in Mean total hospital days with 95% CI

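### SAP sections 10 and 13 compare the strategies only among admissions with an *included antibiotic*, an undefined set that preauthorization can shrink and review at about 72 hours largely cannot

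*Combined protocol and SAP*

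**What the plan says.** - **Analysis set.** SAP section 10 places Tables 1 to 3 for DOT under "Among admissions with an included antibiotic, by hospital". SAP section 13 says "Each of Total hospital days, death, and ICU admission will be summarized by hospital in 3 tables" and then applies "Among admissions with an included antibiotic". Table 3 in each section holds the three contrasts: each strategy against the historical year, and the strategies against each other. In section 13, Table 3 lists differences for ICU admission and total hospital days only, so death is summarized but has no listed contrast.
- **Zero rule.** Section 10 gives DOT 0 to an admission that did not receive a given drug, but the rule sits inside the restricted set. The DOT models follow in the same section with no population of their own.
- **The term.** *Included antibiotic* is never defined. SAP section 6 sets it against an *other* category: "Number of admissions by hospital that received an “Included antibiotic” or “other antibiotic". Table 2 of section 10, under the same restricting line, reads "Period 1 (all admissions with an antibiotic of interest".
- **Strategy 1** (protocol 4.1.4): "If the pharmacist denies the use of the targeted antibiotic, the pharmacist will provide recommendations for alternative antibiotics for the specific clinical scenario".
- **Strategy 2** (protocol 4.1.4): the pharmacist reviews about 72 hours, plus or minus 24, after the order.
- **Other denominators.** Protocol 9.4.2 lists "ADT data for admit/discharge dates for all patients", SAP section 6a counts all unique admissions per hospital and period, and the exploratory objective refers to "traditional (DOT/patient-days) outcomes". No SAP outcome table uses all admissions or patient-days.

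**The concern.** The denominator depends on an event that one strategy is designed to change. A request denied under Strategy 1 can mean that the drug is never given. By the time of a Strategy 2 review the drug has normally been given, so the admission has already qualified. The historical year reflects receipt without either study strategy. The groups in Table 3 can therefore differ in composition because of the strategy. Adjusting for demographics cannot bring back admissions that were left out.

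This bears on the study's own hypotheses. Secondary hypothesis 6 expects preauthorization to reduce overall use less because it does not shorten therapy. On that reasoning its effect comes largely through courses that never start, and those are the courses this denominator can remove. For hospital days, ICU admission and death, the patients who may leave the summaries are those refused the drug.

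**Working it through.** **1. The plan's own figure.** The only related figure is the power statement in protocol 9.1: 3000 patients per intervention period, 0.50 against a proportion 0.05 away, alpha 0.05, 97% power. With a two-sided test and pooled null variance:
- null SE = √(2 × 0.525 × 0.475 / 3000) = 0.01289
- alternative SE = √((0.50 × 0.50 + 0.55 × 0.45) / 3000) = 0.01288
- power = Φ((0.05 − 1.96 × 0.01289) / 0.01288) = Φ(1.92) = 97.3%

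The figure reproduces. Its basis is 600 admissions a month, or 3600 in six months, and its example endpoint is the proportion with no DOT. That reads as an all-admissions denominator, not the restricted one. If 50%, 40% or 20% of 3600 admissions qualified (assumed), the same formula gives 85%, 77% or 48%.

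**2. Inputs for the selection effect.** From protocol 9.1: 3600 admissions per hospital-period. Assumed, since the documents give no such rates:
- 20% of admissions have a targeted request (720) and 30% get alternative drugs only (1080)
- 4 targeted DOT per recipient, and denial unrelated to course length
- 20% of requests denied under Strategy 1 (144 denied, 576 approved), none in the comparator period
- no other effect of either strategy

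**3. All admissions.** Comparator: 720 × 4 / 3600 = 0.80 DOT per admission. Strategy 1: 576 × 4 / 3600 = 0.64. The change is -20%, which is the true effect.

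**4. Targeted-only reading.** Comparator: 2880 / 720 = 4.0. Strategy 1: 2304 / 576 = 4.0. The change is 0%. The share receiving any targeted drug is 720/720 and 576/576, so it is 100% in every group by construction. For denial of 10% to 30%, the restricted result stays at 0% against a true -10% to -30%.

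**5. Targeted-plus-alternative reading.** The comparator set is 720 + 1080 = 1800, with mean 2880 / 1800 = 1.60. Under Strategy 1 the set is 576 + 1080 + 144a, where a is the share of denied patients given a listed alternative:

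| a | Set | Mean targeted DOT | Change |
|---|---|---|---|
| 100% | 1800 | 2304/1800 = 1.280 | -20.0% |
| 80% | 1771.2 | 2304/1771.2 = 1.301 | -18.7% |
| 50% | 1728 | 2304/1728 = 1.333 | -16.7% |

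At a = 50%, denial of 10% to 30% gives -8.2% to -25.5%.

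**6. Death, with no true effect.** Assume mortality of 6% in approved patients and 2% in denied and alternative-only patients.
- Targeted-only: comparator (576 × 0.06 + 144 × 0.02) / 720 = 5.2%; Strategy 1 6.0%.
- Targeted plus alternative, a = 50%: comparator (34.56 + 2.88 + 21.6) / 1800 = 3.28%; Strategy 1 (34.56 + 1.44 + 21.6) / 1728 = 3.33%.

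The false difference is 0.8 percentage points on the first reading and about 0.05 on the second.

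**The case against.** The strongest reply is that the term probably covers targeted and alternative drugs. The restricting line follows lists of both classes, Table 2 uses the wider phrase, and the protocol population is patients prescribed either class. A denial comes with a recommended alternative, and the listed alternatives are broad, so most denied patients may stay in with targeted DOT 0. This stands, and it limits the size of the problem. It does not settle it: SAP section 6 separates included from other drugs, and section 8 pairs included-antibiotic admissions without an intervention with intervention admissions, although interventions concern only targeted drugs.

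Stronger readings that the documents do not support:
- *All denied patients drop out.* This needs the targeted-only reading. Even then, off-hours orders are reviewed the next morning for continuation, so some patients receive the drug before review. The eligible window is 11 × 5 = 55 of 168 weekly hours.
- *The sign of the DOT effect reverses.* This needs the targeted-only reading and preferential denial of short courses. For example, take 30 courses of 2 days and 70 of 5 (410 DOT, mean 4.10) and deny 20 short ones. Total DOT falls 9.8% to 370, while the mean among the 80 left rises 12.8% to 4.625. Nothing in the documents indicates such a pattern.
- *The historical year is unselected.* It falls under the same restricting line. What differs is only that no study strategy acted on receipt.
- *Table 1's intervention split biases the contrasts.* It is a descriptive summary. Table 3 compares whole strategies.
- *The death contrast is biased.* Table 3 lists none; only the death summaries are affected.

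It is also fair that these outcomes are secondary in a feasibility study, that the plan admits limited ability to show definitive change in them, and that the section 6 counts would reveal a shift in the treated fraction. None of this supplies a corrected contrast.

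**Conclusion.** The concern holds in limited form. As written, the DOT, hospital-days and ICU contrasts and the death summaries condition on a post-assignment event that Strategy 1 can change and Strategy 2 largely cannot, and neither limitations section acknowledges it. The primary feasibility summaries are unaffected.

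The size of the bias cannot be derived from the documents. On the stated assumptions it runs from none (wider reading, every denied patient given a listed alternative) to complete masking of a 20% fall in targeted DOT (targeted-only reading). Intermediate cases on the wider reading lose one to three percentage points of that fall. The 0% result rests on denial being unrelated to course length, and every rate except the admission count is assumed.

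**What to change.** - Define *included antibiotic* in the SAP and use one term throughout sections 6, 8, 10 and 13.
- Run Table 3 and the DOT models on all admissions in each hospital-period (the section 6a count), with DOT 0 for non-recipients. Also report DOT per patient-days.
- Give hospital days, ICU admission and death for all admissions as well.
- Keep the antibiotic-restricted set as a descriptive or sensitivity analysis.
- Add the selection to the SAP limitations.
- The Table 1 split may stay if labelled descriptive and not a comparison of strategies.

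**Cost.** SAP wording and reprogramming. Protocol 9.4.2 already lists admission data for all patients and pharmacy data for all antibiotics. Because protocol 4.1.2 ties record collection to patients prescribed a listed drug, confirm that all admissions reach the analysis dataset. Per-admission effects will look numerically smaller: in the illustration with every denied patient given a listed alternative, the same 20% fall is 0.16 DOT per admission (0.80 to 0.64) over all admissions, against 0.32 (1.60 to 1.28) in the wider restricted set.
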